### Interim analysis

We have no plans to perform or publish interim analyses.

### Methods for additional analyses (e.g. subgroup analyses)

No additional analyses are planned.

### Methods in analysis to handle protocol non-adherence and any statistical methods to handle missing data

We analyse the data of all patients who meet the inclusion and exclusion criteria, complete the study without dropout within 72 h after surgery. In case of missing data during the study, patients will be excluded. In the case of dropping out from the study, no further data will be collected; however, the exact reason for withdrawal will be documented. We expect a withdrawal rate of 20% per group.

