## Introduction

### Background and rationale

Postoperative pain after spinal surgery is debilitating for the patients due to its severe intensity. As the spine is located at the centre of the body to support body weight, severe postoperative pain hinders upper body elevation and gait, which can lead to various complications, including pulmonary deterioration and pressure sores [1, 2]. Effective control of postoperative pain is important for the prevention of such complications and for fast rehabilitation [3, 4].

Preemptive multimodal analgesia is often performed using acetaminophen and nonsteroidal anti-inflammatory drugs (NSAID) [5, 6]. However, NSAIDs have a risk of complications, such as renal toxicity, bleeding tendency, and cardiac events, limiting their use in the elderly or in patients with pre-existing renal insufficiency [7, 8]. NSAID use following spinal fusion has also been reported to increase the rate of nonunion [9]. In contrast, gabapentinoids including gabapentin and pregabalin are relatively safe for patients with renal or cardiac risk factors, do not hinder fusion after spinal surgery, show opioid-sparing effects, and decrease the adverse effects of intravenous patient-controlled analgesia (IV PCA) [10, 11]. Due to these advantages and their efficacy, gabapentinoids are widely used for the management of postoperative pain after various surgeries [12–14].

Pregabalin binds to the α2-δ protein subunit of presynaptic voltage-gated calcium channels in both the central and peripheral nervous systems, and it has a superior pharmacodynamic and pharmacokinetic profile to that of gabapentin [15]. It is a more potent and more effective analogue of gabapentin [16]. However, gabapentinoids are associated with several adverse effects, including sedation, dizziness, and peripheral oedema, which are known to be dose-dependent [17]. There is currently some controversy regarding the optimal safe dose of gabapentinoids.

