### Eligibility criteria

Patients undergoing spinal surgery for degenerative lumbar disorders will be recruited from the Department of Orthopaedic Surgery, at Ajou University Hospital. Identified patients will be approached for inclusion in the study based on the inclusion/exclusion criteria described below.

Inclusion criteria are as follows: age 19 years or older, patients undergoing spinal surgery for degenerative lumbar disorders, and voluntary agreement to participate in the study after receiving sufficient explanation.

Exclusion criteria are as follows: minors under the age of 19 years, patients assigned to American Society of Anesthesiologists classification class 3–6, previous frequent dizziness or headaches, active alcohol or drug usage, having taken any analgesics daily or within 48 h before surgery, impaired renal (glomerular filtration rate < 60 mL/min/1.73 m^2^) and/or hepatic function (Child Pugh classification B and C), diagnosed with and treatment for anxiety or depressive disorders, and coverage from worker’s compensation insurance or car insurance.

Patients with severe adverse reactions to our drug of interest, such as dizziness, drowsiness, or peripheral oedema, will be excluded. Patients with any postoperative complications including infection, nerve injury, hematoma, metal implant-related problems, and death, will also be excluded.

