### Criteria for discontinuing or modifying allocated interventions

Participants who present with severe drowsiness, dizziness, visual disturbance, or swelling that precludes the use of pregabalin will discontinue the trial and stop taking their allocated treatment. Participants who develop infection, nerve injury, hematoma, or metal-related complications following surgery or those who request discontinuation will also be excluded from the trial.

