### Plans to promote participant retention and complete follow-up

The intervention will occur during the first 72 h after surgery and will be monitored closely by the study team throughout that period. Evaluation of postoperative pain using the VAS and postoperative complications are part of the routine postoperative patient examination. Patients do not need to adhere to any other specific tasks, and there is no outpatient clinic follow-up as part of the study, so there will be no difficulties in completing the evaluation.

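### The completers-only analysis rule takes patients who withdraw for severe side effects out of the arm comparison, which understates harms and breaks the randomised efficacy comparison

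*Protocol article*

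**What the plan says.** All references are to the Protocol article.

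- **Analysis set.** The section on non-adherence and missing data restricts the analysis to patients who meet the entry criteria and "complete the study without dropout within 72 h after surgery. In case of missing data during the study, patients will be excluded".
- **After dropout.** The same section says: "In the case of dropping out from the study, no further data will be collected; however, the exact reason for withdrawal will be documented". It expects 20% of each group to withdraw.
- **Leaving treatment means leaving the trial.** Under the criteria for discontinuing allocated interventions, patients with drowsiness, dizziness, visual disturbance or swelling severe enough to rule out pregabalin "will discontinue the trial and stop taking their allocated treatment". Patients with listed surgical complications, and those who ask to stop, are excluded as well.
- **Eligibility criteria.** This section adds: "Patients with severe adverse reactions to our drug of interest, such as dizziness, drowsiness, or peripheral oedema, will be excluded". Its next sentence excludes patients with postoperative complications, including death.
- **Timing.** Sequence generation places randomisation one day before surgery, so on-treatment reactions and postoperative complications come after it.
- **Harms as outcomes.** The Objectives include safety by dose. The statistical methods section compares sedation, dizziness, headache, visual disturbance and swelling between groups by chi-squared test. No other analysis set is stated, and no additional analyses are planned.

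**The concern.** The Background describes adverse effects of gabapentinoids "including sedation, dizziness, and peripheral oedema, which are known to be dose-dependent". The article therefore expects more of these effects at higher doses. It compares them between arms, yet removes from the analysed population the patients in whom they are bad enough to end treatment. A patient's inclusion depends on an outcome that the drug can affect.

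Two results are at stake. The safety comparison across doses, which is half of the stated objective, would omit the events that matter most for choosing a dose. The efficacy comparison would be between those who tolerated each dose, and those groups need not be comparable even though the randomised groups were. This is a stated rule, so it is not a detail left to an analysis plan.

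**Working it through.** **1. The plan's own numbers.** The sample-size section asks for 28 analysable patients per group and allows about 15% loss: 28 / 0.85 = 32.9, rounded up to 33 per group and 132 in total. This reproduces. At the 20% withdrawal given in the missing-data section, 132 × 0.20 = 26.4, so about 26 randomised patients would be left out and 33 × 0.80 = 26.4 per arm would remain.

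Taking the article's effect size (0.448) and alpha (0.0167) as stated, one-way ANOVA power from the noncentral F distribution is about 94.0% with 26.4 per arm. It is 98.2% with all 33 kept, before any dilution from patients who stopped. Lost power is therefore minor; the issue is selection.

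**2. Effect on the harms comparison.** The documents give no event rates, so all rates here are assumptions. If a share *a* of an arm has the event at any grade, and a share *s* has it severely enough to be removed, the rate among those analysed is (a − s) / (1 − s).

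Assume dizziness of 10% on placebo with none severe, and 30% at 75 mg. The true difference is 20 points.

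| Removed at 75 mg | Rate seen at 75 mg | Difference from placebo |
|---|---|---|
| 2% | 0.28 / 0.98 = 28.6% | 18.6 points |
| 5% | 0.25 / 0.95 = 26.3% | 16.3 points |
| 12% | 0.18 / 0.88 = 20.5% | 10.5 points |

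A second assumption lets placebo patients be removed too, with the same fraction of cases severe in both arms:

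| Fraction severe | 75 mg | Placebo | Difference |
|---|---|---|---|
| 25% | 0.225 / 0.925 = 24.3% | 0.075 / 0.975 = 7.7% | 16.6 points |
| 50% | 0.15 / 0.85 = 17.6% | 0.05 / 0.95 = 5.3% | 12.4 points |
| 75% | 0.075 / 0.775 = 9.7% | 0.025 / 0.925 = 2.7% | 7.0 points |

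The difference shrinks in every row; only the amount depends on the assumption.

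**3. Effect on the efficacy comparison.** Suppose there is no true effect, and removal of a share *d* of an arm has correlation ρ with pain. The mean among those kept shifts by ρ·φ(z_d) / (1 − d) SD, where z_d is the normal quantile of *d*. With 5% removed on placebo and 20% at 75 mg, the shifts per unit ρ are 0.1031 / 0.95 = 0.109 and 0.2800 / 0.80 = 0.350. For ρ from 0.2 to 0.5 the false difference is 0.05 to 0.12 SD. With 10% and 30% removed it is 0.06 to 0.15 SD. With equal removal and the same mechanism in every arm it is zero. The sign depends on whether those removed would have had more or less pain.

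**The case against.** The main objection is that the concern is easily overstated. A reader might infer any of the following.

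- **The severe events vanish from the trial.** They do not. The adverse-event section records all events in the case report form and reports severity and causality, and the reason for withdrawal is kept. What they leave is the comparison between arms.
- **Severe events will read zero in every arm.** The discontinuation section removes only reactions that preclude pregabalin, so severe but tolerated ones stay. The Eligibility sentence lacks that limit, but it could refer to earlier reactions to the drug; only the complications sentence after it is plainly post-randomisation. Headache is in neither list.
- **Removal differs by arm by construction.** One rule applies to all arms. Dose dependence makes unequal removal likely, not certain. All arms receive fentanyl, and if pregabalin spares opioid, opioid-related sedation or dizziness in the placebo arm could offset part of the gradient. The 15% and 20% losses are stated per group and are not evidence of imbalance.
- **The Discussion's anticipated conclusion is an artefact of the rule.** That sentence ends by referring to the 25 mg dose. If 15% of that arm had dizziness and 3% were removed, the rate would move only to 0.12 / 0.97 = 12.4%.

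The efficacy bias is also modest beside the planning means, which span (105.2 − 95.3) / 10 = 0.99 SD.

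These points limit the wording and the size. They do not remove the defect, because nothing in the article returns the withdrawn patients to the chi-squared comparison or to the efficacy analysis. That one population serves both is an inference, but it is the only population stated.

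**Conclusion.** The concern holds in this form: as written, events that cause withdrawal drop out of the between-arm safety comparison, and efficacy is compared among completers instead of among the randomised groups. Harms are understated wherever such events occur. The dose gradient is probably flattened, on the article's own premise of dose dependence.

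The size cannot be fixed from the documents. Under the assumed rates, a true 20-point difference is seen as anything from 18.6 down to 7.0 points, and a null efficacy effect acquires a false difference of 0.05 to 0.15 SD. If removal had the same rate and mechanism in all arms, the efficacy bias would disappear, but the severe events would still go uncounted. The rule should be corrected promptly, because outcomes not collected after withdrawal cannot be recovered later.

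**What to change.** 1. **Efficacy.** Make the primary analysis all randomised patients as allocated, using all available data. Use a missing-data method suited to each outcome (for example a mixed model for the repeated VAS scores; rescue counts need their own method) and a sensitivity analysis for the missing-data assumption. Keep the completers' analysis as a sensitivity analysis.
2. **Safety.** Analyse everyone who took at least one dose, and count events that led to discontinuation.
3. **Follow-up.** Separate stopping study drug from leaving the trial. Collect VAS, opioid use and adverse events to 72 h unless consent is withdrawn.
4. **Consistency.** Reconcile the eligibility, discontinuation and missing-data sections so that post-randomisation events are not exclusions from analysis, and state what the adverse-reaction sentence under eligibility means. The clinical stopping criteria stay as they are.

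**Cost.** Item 3 reverses a stated data-collection rule, so it changes conduct as well as wording. The added work should be small, since the retention section says: "Evaluation of postoperative pain using the VAS and postoperative complications are part of the routine postoperative patient examination". The efficacy contrast may be somewhat diluted by patients who stopped early. The unblinding section allows the code to be broken for severe reactions, complications and requests to stop, so some later VAS scores may be unblinded. These should be flagged and examined in a sensitivity analysis.

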### Sample size

The prior calculation of the sample size indicated that at least 28 subjects were required for each group. For calculation, the software G*Power 3.1.9.7 was used with a statistical power of 0.95 at an effect size of 0.448 with an alpha level of 0.0167. The effect size was determined based on a previous study [18]. In this study, three groups—those treated with placebo, pregabalin 75 mg, and pregabalin 150 mg—each comprised 28 participants. The groups were compared based on their PCA usage, with mean values of 95.3, 96.6, and 105.2 respectively, and an approximate standard deviation of 10. For the purposes of this study, which involves four instead of three groups, a fourth hypothetical group was considered with the mean value of 96.6, which is the median value of the three established groups. Based on this data, Cohen’s *f* was calculated, resulting in an effect size of 0.448. To compare the four groups through Bonferroni’s test, the alpha level was set at 0.05 divided by 4, which is 0.0167. When calculated based on these parameters, the total sample size needed is found to be 112, and the number of participants needed per group is 28. Considering a follow-up loss of approximately 15%, 33 participants per group would be required, resulting in a total of 132 participants needed for the study.

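### The sample size allows for about 15% loss, but the analysis section expects 20% withdrawal, which leaves about 26 evaluable patients per group against a stated minimum of 28

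*Protocol article*

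**What the plan says.** Two sections of the protocol article give a figure for patients lost to the analysis.

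- **Sample size.** The calculation "indicated that at least 28 subjects were required for each group", with G*Power "used with a statistical power of 0.95 at an effect size of 0.448 with an alpha level of 0.0167". It then adds an allowance for loss: "Considering a follow-up loss of approximately 15%, 33 participants per group would be required, resulting in a total of 132 participants".
- **Methods in analysis to handle protocol non-adherence and any statistical methods to handle missing data.** "We expect a withdrawal rate of 20% per group". The same section restricts the analysis to eligible patients who finish the 72 hours without dropping out, excludes patients with missing data, and stops data collection at dropout.

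The article does not explain why the two rates differ, and does not say that they measure different things.

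**The concern.** The allowance for loss is there so that the number analysed still meets the number the power calculation requires. That works only if the rate used for the allowance is the rate the investigators expect. Here the allowance uses about 15% and the analysis section expects 20%. Because the analysis is limited to completers without missing data, the higher rate takes patients directly out of the sample on which power depends.

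At stake are the stated minimum per group and the stated power of 0.95. If the 20% is meant, the protocol predicts that it will miss both, and a reader cannot tell which figure to hold the trial to.

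**Working it through.** **Inputs** (all from the protocol article)

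- Evaluable number required: 28 per group, 112 in total (Sample size).
- Power 0.95, Cohen's f 0.448, alpha 0.0167 (Sample size).
- Loss allowed for: about 15%, giving 33 per group and 132 in total (Sample size).
- Withdrawal expected: 20% per group (non-adherence and missing data section).
- Four groups, 1:1:1:1 (Sequence generation).

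**Step 1: reproduce the plan's figures.** The method is the one-way ANOVA omnibus F test with k = 4 and N = 4n, noncentrality f² x N, and degrees of freedom k − 1 and N − k.

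- At n = 28, N = 112 and the noncentrality is 0.448² x 112 = 22.48, with 3 and 108 degrees of freedom. Power is 0.955.
- At n = 27, power is 0.946, below 0.95. So 28 is the smallest number per group that meets the target, as the article says.
- Allowance for loss: 28 / (1 − 0.15) = 32.94, rounded up to 33 per group, and 4 x 33 = 132. This also agrees.

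**Step 2: apply each loss rate to 33 per group.**

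| Loss | Evaluable per group | Evaluable in total | Meets 28 per group? |
|---|---|---|---|
| 15% | 33 x 0.85 = 28.05 | 112.2 | Yes, with almost no slack |
| 20% | 33 x 0.80 = 26.4 | 105.6 | No |

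**Step 3: power at the expected evaluable number, on the plan's own f and alpha.**

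| Evaluable per group | Noncentrality | Power | Against 0.95 |
|---|---|---|---|
| 28 | 22.48 | 0.955 | +0.005 |
| 26.4 | 0.448² x 105.6 = 21.19 | 0.940 | −0.010 |
| 26 | 0.448² x 104 = 20.87 | 0.936 | −0.014 |

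**Step 4: the number that would hold 28 evaluable at 20%.** 28 / (1 − 0.20) = 35 per group, 140 in total, which is 8 more than planned.

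**The case against.** **The two rates may not be the same quantity.** One section speaks of follow-up loss and the other of withdrawal. The difference in wording is real, but under the stated analysis rule both remove the patient from the analysed set, so both bear on the same 28. If the 20% does not include patients excluded for missing data, the shortfall is larger. The article does not say.

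**The consequence is small.** This stands. The power target of 0.95 is high, and 0.936 to 0.940 is still good power on the plan's own inputs.

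A reader might infer three stronger things that the document does not support.

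1. *That the mismatch brings power down to about 0.84 or 0.82.* Those values come mostly from other errors in the Sample size section. The quoted means (95.3, 96.6, 105.2 and the hypothetical 96.6) have mean 98.425 and squared deviations summing to 62.33. With the SD of about 10, f = √(62.33/4) / 10 = 0.395, not 0.448. Also, 0.05 divided by 4 is 0.0125, not 0.0167. With f = 0.395 and alpha 0.0167, power is already 0.877 at 28 per group and 0.844 at 26. With alpha 0.0125 it is 0.854 and 0.817. Going from 28 to 26 therefore accounts for only 3.3 to 3.7 points. The rest is a separate matter.
2. *That the retention section is a third contradicting figure.* It says "there will be no difficulties in completing the evaluation", but it gives no rate. Its argument is that patients have no extra tasks and no outpatient visits. A patient can be easy to assess and still be withdrawn for an adverse reaction, a surgical complication or at their own request, as the discontinuation section provides. That optimism sits awkwardly beside an allowance of 15% or 20%, but it does not contradict either.
3. *That analysing all randomised patients with their available data would recover most of the loss.* Data collection stops at dropout, so an early withdrawal has no complete 72-hour total of patient-controlled analgesia, the type of outcome (PCA usage) on which the sample size was based. How much would be recovered depends on when patients withdraw, which the article does not give.

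**Conclusion.** The inconsistency is real and lies between two stated figures, 15% and 20%. Under the 20% expectation and the completers-only rule, about 26 patients per group are evaluable, roughly two short of the stated minimum of 28. Power is then about 0.94 and not the stated 0.95.

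This rests on three assumptions: that the 20% applies equally to all four groups, as the article says; that every withdrawn patient leaves the analysis, which the stated rule implies; and that f = 0.448 and alpha = 0.0167 are taken as given. It is worth correcting because a stated minimum fails on the protocol's own expectation. It does not by itself show a seriously underpowered trial.

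**What to change.** State one loss rate and use it in both the Sample size section and the non-adherence and missing data section.

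- If 15% is the real expectation, replace the 20%. The figures of 33 and 132 then stand on the plan's inputs.
- If 20% is the real expectation, keep 132 patients and state that about 26 per group are expected to be evaluable, with power of about 0.94 at f = 0.448 and alpha = 0.0167. Recompute that power if the effect size and alpha in the Sample size section are corrected.

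The retention section needs no figure. The change is to the text only: the stated power becomes slightly less favourable and no extra patients are needed. Going to 35 per group (140 in total) would restore 28 evaluable at 20% loss, but a gap of 1 to 1.4 points does not require it.

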### Plans to give access to the full protocol, participant-level data, and statistical code

Access to participant-level deidentified data and statistical data will be considered by the corresponding author upon reasonable request.

## Oversight and monitoring

### Composition of the coordinating centre and trial steering committee

The coordinating centre is composed of clinicians at the Department of Anesthesiology and Pain Medicine and the Department of Orthopaedic Surgery of Ajou University Hospital, including the principal investigator. The centre consists of the principal investigator ([name]) and two investigators ([name] and [name]) who are responsible for recruiting the patients and conducting the study. The trial steering committee will check and discuss whether the study is being conducted appropriately the day after enrolment of each patient.

### Composition of the data monitoring committee, its role and reporting structure

In this study, the research team determined that an independent data monitoring committee is not necessary, as there will be no interim analysis, patients involved have non-critical conditions and will undergo treatment for a relatively brief period, and the drug under investigation has a well-characterized safety profile with no known harm to patients. Furthermore, due to the brief intervention duration and limited sample size, no interim analysis will be conducted.

